**Sample size and design for Baseline and End line Surveys**

Clearly it would be impossible to conduct an in-depth evaluation of all population in the community based nutrition program. However, the assessment must be robust, scientifically valid and plausible within existing time frames. Therefore a representative sample size has been calculated separately for both baseline & endline surveys and embedded Randomized control trial. Details of both estimations are as under:

Below mentioned formula for sample size estimation for baseline and endline cross sectional surveys were used from MI & CDC manual [6] to calculate the sample size. Prevalence of stunting (49% Sindh) from NNS 2011, 80% power to detect 10% reduction in prevalence of stunting during the three-year implementation of the Stunting Prevention Programme with a significance level of 0.05 was considered for sample size estimation.

[figure not shown]

Assumptions:

- p1 is stunting rate at baseline without intervention at baseline survey =49%
- p2 is estimated stunting rate after intervention at end line survey
- DEFF : The estimated design effect = 1.5
- α : Level of significance (“alpha”), usually 0.05 or 5% (corresponds with 95% confidence interval)
- 1- β: Power, usually 0.8 (80%) Assumed 10% reduction in stunting

For estimating impact of the interventions each group will require 3200 participants. To account for dropouts and data errors, the sample size will increased by 10% giving a new total of 7040 study participants (3520 participants per group). Information will be collected from 4,200 households at baseline and at endline. The study participants from selected households will be pregnant women, lactating women and children under five years. Two stage cluster sampling technique will be used. LHW catchment areas of 29 UCs will be treated as a cluster for intervention group and control group.

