**Methodology for Cluster Randomized Controlled Trial**

**Sample Size Estimation:**

A union council has been taken as the cluster for the estimation of sample size for RCT. The following three sample sizes were calculated to detect a range of differences in nutritional status for all study participants;

1. Pregnant and Lactating Women: To calculate sample size for PLW, we aimed to achieve a 25% difference in the prevalence of low birthweight. With a power of 0.80 and a statistical significance of 0.05, we calculated that a sample size of 160-170 per cluster would be sufficient for analyzing the reduction in low birthweight. A total of 2,000 PLW will be enrolled in the trial.
2. Children 6-23 months: Sample size for children aged 6-23 months was calculated to detect a 10% difference in risk reduction in stunting among the intervention group compared to the control group. A sample size of 70-75 children per cluster was estimated with a statistical significance of 0.05, power of 0.80, and an intra-cluster correlation of 0.02. A total of 900 children, 6-23 months old will be enrolled in the trial.
3. Children 24-59 months: To detect a 10% difference in risk reduction in stunting among the intervention group compared to the control group, a sample size of 90-95 children per cluster was drawn, with a statistical significance of 0.05, power of 0.80, and an intracluster correlation of 0.02. A total of 1100 children aged 24-59 months will be enrolled in the trial.

The total sample size will be taken from 12 union councils which will be randomly selected from the list of 29 union councils, 6 union councils for intervention group and 6 union councils for control group.

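### The cluster trial's stated 80% power for stunting does not follow from its own inputs: at 49% control prevalence and an absolute 10-point fall, 6 union councils per arm give about 41-52%

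*Protocol*

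**What the plan says.** All design inputs stand in the protocol's Sample Size Estimation paragraph for the nested cluster randomized trial.

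- Unit of randomization: "A union council has been taken as the cluster for the estimation of sample size for RCT".
- Clusters: 12 union councils drawn from 29, with "6 union councils for intervention group and 6 union councils for control group".
- Effect, in both child cohorts: "to detect a 10% difference in risk reduction in stunting among the intervention group compared to the control group". Whether the 10% is absolute or relative is not said.
- Ages 6-23 months: "A sample size of 70-75 children per cluster was estimated with a statistical significance of 0.05", with "power of 0.80, and an intra-cluster correlation of 0.02. A total of 900 children, 6-23 months old will be enrolled in the trial".
- Ages 24-59 months: "a sample size of 90-95 children per cluster was drawn", with the same significance level, power and ICC, and 1,100 children in total.
- Low birth weight: "we calculated that a sample size of 160-170 per cluster would be sufficient for analyzing the reduction in low birthweight". No ICC or baseline rate is given.

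The paragraph gives no control-group stunting prevalence, sidedness or formula. The baseline and endline survey calculation uses "Prevalence of stunting (49% Sindh) from NNS 2011", and the Preamble gives a national figure of 44%. Risk of stunting is the trial's primary outcome.

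**The concern.** With a fixed number of clusters, adding children within each cluster yields diminishing returns. The effective sample size per arm cannot exceed the number of clusters divided by the ICC, here 6/0.02 = 300. A 10-point difference around 49% needs more than 300 independent children per arm, so the stated number of clusters, ICC and power cannot all hold at that prevalence.

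This is the only power justification given for the trial's primary outcome. If it is wrong, a non-significant result is much less informative than the protocol implies, because the trial would miss the effect it says it is sized for about half the time or more.

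**Working it through.** **Inputs.** From the trial's sample size paragraph: k = 6 clusters per arm, ICC = 0.02, alpha = 0.05, and totals of 900 and 1,100. Assumed: control prevalence 49% (from the survey calculation), an absolute fall to 39%, and a two-sided test.

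**1. The stated sizes agree with each other.** 900/12 = 75 and 1,100/12 = 91.7 per cluster, matching 70-75 and 90-95. The question is whether they give 80% power.

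**2. Children needed without clustering.** n per arm = (1.96 + 0.84)² × [p1(1−p1) + p2(1−p2)] / (p1−p2)² = 7.849 × (0.2499 + 0.2379) / 0.01 = 383. With a pooled variance under the null it is 386.

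**3. Design effect,** DE = 1 + (m−1) × ICC.
- 6-23 months: 1 + 74 × 0.02 = 2.48; effective n = 450/2.48 = 181 per arm.
- 24-59 months: 1 + 90.7 × 0.02 = 2.81; effective n = 550/2.81 = 195 per arm.

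**4. Power,** Φ(0.10/SE − 1.96) with SE = √(0.4878 / effective n). The second version uses a noncentral t with 12 − 2 = 10 df, which suits 12 clusters better.

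| Cohort | SE | Normal | t, 10 df |
|---|---|---|---|
| 6-23 months (m = 75) | 0.0518 | 48-49% | 41% |
| 24-59 months (m = 91.7) | 0.0500 | 51-52% | 44% |

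The normal ranges reflect pooled or unpooled variance. At the ends of the stated cluster sizes the results hardly move: m = 70 gives about 47-48% or 40.5%, and m = 95 about 52% or 44.5%.

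**5. Ceiling.** As m grows without limit, effective n tends to 300 per arm, below the 383 required. SE = √(0.4878/300) = 0.0403, so power = Φ(2.48 − 1.96) = about 70% (normal) or 61% (t).

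**6. Sensitivity to the borrowed prevalence.**
- 44% to 34%: n = 7.849 × (0.2464 + 0.2244)/0.01 = 370, still above 300. Power at the stated sizes is about 49-53% (normal); the ceiling is 71% (normal) or about 63% (t).
- 30% to 20%: about 60-63% (normal) at m = 75 and 92. The normal ceiling is 81%, so the statement about every cluster size no longer holds there.
- To reach 80% at the stated sizes, control prevalence would have to be about 18-20% or less (or the mirror value above 90%).

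**7. Relative reading.** 49% to 44.1% gives 13-16% power at the stated sizes.

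**8. Difference detectable at 80% power from 49%.**
- 6-23 months: normal, 2.80 × √[(0.2499 + 0.3465 × 0.6535)/181.5] = 0.1435, or 14.4 points; t, about 15.9 points.
- 24-59 months: normal, 2.80 × √[(0.2499 + 0.3515 × 0.6485)/195.5] = 0.1385, or 13.9 points; t, about 15.3 points.

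**The case against.** The strongest objection is that 49% is borrowed: the trial's own paragraph states no prevalence. This is right, and it makes the ceiling claim conditional. It holds at both prevalences the protocol gives, 49% and 44%, but not at about 30% or below. The shortfall at the stated cluster sizes is much less sensitive, since even 30% leaves power near 60%.

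Sidedness is also unstated. A one-sided 0.05 test at 49% gives about 60-64% (normal) at the stated sizes, with a ceiling just under 80%. At 44% the one-sided ceiling is Φ(0.10/√(0.4708/300) − 1.645) = 81%. The ceiling claim therefore assumes a two-sided test, which the survey section implies by pairing alpha with a 95% confidence interval. The shortfall at the stated sizes remains either way.

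Baseline adjustment or the quarterly measurements might recover some power. The sample size paragraph does not invoke either, so they do not rescue the calculation as stated. The trial is also nested in a larger double-difference evaluation and is not the only evidence on stunting, which limits the consequence but does not correct the figure.

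Two stronger readings are tempting. A reader might infer that the total of 12 clusters was entered as the number per arm. At 49%, 12 per arm requires 383 × 0.98/(12 − 383 × 0.02) = 86 per cluster, which is in neither stated range. Leaving the ICC out and adding 10% gives 383/6 × 1.1 = 70, which fits the younger cohort equally well. The origin is not established. A reader might also infer that the low-birth-weight calculation fails. With no ICC or baseline rate stated, power for a 25% relative reduction could run from 22% to 99% over ICC 0-0.02 and baselines of 15-35%, so no failure is shown. The mention of lactating women in that count is a wording inconsistency, because the trial description and the recruitment section refer to women enrolled in pregnancy and followed to birth.

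**Conclusion.** The 80% power statement is wrong as written for both child cohorts. Actual power is roughly half to two-thirds of the stated figure, conditional on 49% control prevalence, an absolute 10-point fall, ICC 0.02 and a two-sided test. The absolute reading is the one favourable to the plan. The limiting factor at the protocol's own prevalences is the number of clusters, not the number of children. No conclusion is drawn about how the error arose or about the power for low birth weight.

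**What to change.** In the trial's Sample Size Estimation paragraph, replace the 80% power statements for both child cohorts with one of the following:

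- the power that 6 union councils per arm deliver for the chosen difference (about 41% and 44% by the t calculation for 49% to 39%); or
- the difference detectable at 80% power, as derived above (about 14-16 points for 6-23 months and 14-15 points for 24-59 months).

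Either way, state the control prevalence used, that the difference is absolute, the sidedness and the method. Adding the ICC and baseline rate behind the low-birth-weight figure would allow it to be checked.

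This is a change of wording and needs no added participants; the cost is a less favourable stated power. It corrects the claim but does not raise the power. Under this calculation, 80% at the stated cluster sizes would take about 12-14 union councils per arm.

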**Study site**

This study will be conducted in 29 Union councils of districts Thatta and Sajawal of Sindh Province. The LHW catchment area of 29 targeted union councils of these districts will be in the intervention group, while remaining uncovered area of these union councils will be in control group. The UC wise details of LHWs, total population as well as covered and uncovered population are attached in annex I.

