**Recruitment of potential participants:**

Children 6-23 and 24-59 months of age and Pregnant or lactating mothers will be potentially eligible cohorts for inclusion in the study and will be identified through the baseline survey being done in the targeted union councils. Pregnant women will be enrolled during first and second trimester of pregnancy, children 6-23 months cohort during 6-18 months and children 24-59 months cohort during 24-54 months of age for minimum exposure of six months. A detailed recruitment form will be filled from each study participant. Detailed physical & anthropometric examination and sport Hb testing will also be done at the time of recruitment.

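### With only six union councils per arm, the nested trial states no balance restriction on the 6:6 allocation, although union-council data that would allow one are in annex I

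*Protocol*

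**What the plan says.** The trial's unit is the union council: "A union council has been taken as the cluster for the estimation of sample size for RCT". The sampling sentence reads: "The total sample size will be taken from 12 union councils which will be randomly selected from the list of 29 union councils". It ends with the split: "6 union councils for intervention group and 6 union councils for control group". No section states stratification, matching, constrained randomisation or a balance criterion.

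On data by UC, the Study site section says: "The UC wise details of LHWs, total population as well as covered and uncovered population are attached in annex I". It also places the 29 UCs in two districts. Under Recruitment of potential participants, eligible women and children "will be identified through the baseline survey being done in the targeted union councils", and anthropometry is taken at recruitment. The order of baseline survey, recruitment and allocation is not given.

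For children aged 6-23 months the stated size is "70-75 children per cluster was estimated with a statistical significance of 0.05, power of 0.80, and an intra-cluster correlation of 0.02". For ages 24-59 months it is "a sample size of 90-95 children per cluster was drawn, with a statistical significance of 0.05, power of 0.80".

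**The concern.** With 12 clusters, one unrestricted draw can easily leave the arms unlike each other in underlying stunting, district, health-worker coverage or the presence of other programmes. The Complementary interventions section says that an EU-funded project will reinforce behaviour change and acute-malnutrition work in most of the UCs, so not in all. With six UCs per arm, a few untypical ones can shift an arm mean by an amount that matters against the effect sought.

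The information needed to limit this is at least partly in hand. The question is therefore whether a better allocation method than the one the text implies is available at low cost. A noisier comparison, and a result that is harder to defend if the arms visibly differ at baseline, are what is at stake.

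**Working it through.** **Inputs**
- 12 UCs, 6 per arm; ICC 0.02; 70-75 children per UC aged 6-23 months and 90-95 aged 24-59 months (trial Sample Size Estimation section).
- Stunting prevalence 49% (survey sample-size section). The trial states no control rate, so using 49% here is an assumption.
- Effect sought: 10%, not said to be absolute or relative. On 49%, these are 10 points or 4.9 points.

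**The plan's own figures.** The totals agree with the cluster sizes: 12 × 75 = 900, and 12 × (90 to 95) = 1,080 to 1,140 against 1,100 stated. Whether these totals give the stated power is a separate question and is not used here. The plan gives no figure for imbalance.

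**Imbalance in underlying stunting, unrestricted 6:6**
- SD between UCs = √(ICC × p × (1 − p)) = √(0.02 × 0.49 × 0.51) = 0.0707, or 7.1 points.
- SD of the difference in arm means = 0.0707 × √(2/6) = 0.0408, or 4.1 points.
- Normal approximation: P(|difference| > 5 points) = P(|Z| > 5/4.08) = 22%; P(> 10 points) = 1.4%.
- Sensitivity to the ICC: P(> 5 points) is 8% at ICC 0.01 and 44% at ICC 0.05.

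**Imbalance in any one UC-level variable.** There are C(12,6) = 924 allocations. All were enumerated over 2,000 simulated sets of UC values.

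| Allocation | Root-mean-square arm difference (in SDs of the variable) | P(> 0.5 SD) |
|---|---|---|
| Unrestricted 6:6 | 0.58 | 41% |
| 3:3 within each of two strata formed on the variable | 0.36 | 18% |
| Best 10% of allocations, 1 variable | 0.05 | 0% |
| Best 10%, 2 variables | 0.14 | 0% |
| Best 10%, 4 variables | 0.26 | 3% |

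On district alone: if the 12 UCs were six from each district (an assumption, since no district counts are given), a 3:3 split arises in 20 × 20 = 400 of 924 unrestricted allocations, or 43%, and is missed in 57%.

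**What this does for stunting.** If the balanced variable has correlation r with UC stunting, perfect balance leaves SD = 4.08 × √(1 − r²):
- r = 0.3: 3.9 points, P(> 5 points) 20%
- r = 0.5: 3.5 points, 16%
- r = 0.7: 2.9 points, 9%

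The protocol gives no such correlation.

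Balancing on measured baseline stunting does more. With the best 10% of allocations at ICC 0.02, treating children as a simple random sample within each UC:
- 70 children per UC: SD about 2.6 points, P(> 5 points) about 6%.
- 165 per UC (both child cohorts: 70-75 plus 90-95 gives 160-170): SD about 2.0 points, about 1%.

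These results concern baseline stunting. The gain at the end of follow-up depends on how well baseline tracks it.

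**The case against.** Four objections have force.

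**The method criticised is inferred.** The words on random selection govern the draw of 12 UCs from 29. How the 12 are then allocated is not described, and the sentence sits in a sample-size section. A reader might infer that the protocol prescribes simple randomisation; it does not use that term. What can be said is that it states no restriction, and that an unrestricted draw is the natural reading. Allocation could be described in another document, but it is a design decision taken before enrolment and the protocol is the place to fix it.

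**Chance imbalance is not bias.** A reader might infer that an imbalance of this size could not be told apart from a treatment effect. That does not follow. The 4.1-point SD is the variance component that the ICC represents, and a valid cluster-level analysis carries it in its standard error. Baseline anthropometry also permits adjustment without restricted allocation. This stands, and it limits the point to precision and credibility.

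**Annex I is not described as holding stunting data.** It is said to list health-worker and population figures. UC stunting would have to come from the baseline survey or recruitment measurements, and nothing says that these precede allocation. The trial is described as running during intervention delivery. This stands, so baseline stunting can be only a conditional part of the fix.

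**The groups are defined in two ways.** The Study site section puts health-worker catchment areas of all 29 UCs in the intervention group and the uncovered areas of the same UCs in control. The trial assigns whole UCs. Until these passages are reconciled, it is unclear what balancing health-worker coverage would mean in a control UC. This also stands and is taken into the fix.

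**Conclusion.** The point holds as a recommended improvement to the design, not as a fault in validity. With no stated restriction and six UCs per arm, true underlying stunting would differ between arms with an SD of about 4.1 points, and by more than 5 points in about 22% of allocations. Five points is half the effect if 10% is absolute and slightly more than the whole effect (4.9 points) if it is relative. These figures rest on the protocol's ICC of 0.02, the assumption that 49% applies to the trial, and a normal approximation. Across ICCs of 0.01 to 0.05 the 22% ranges from 8% to 44%.

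A reader might also infer that stratified or constrained allocation would abolish the imbalance. The calculations do not support that. Restriction nearly removes imbalance only in the few variables it uses, and lowers imbalance in stunting only as far as those variables predict stunting.

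**What to change.** First reconcile the Study site definition of intervention and control with allocation by UC.

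Then, in the trial's methodology section, state that the 12 UCs are allocated 6:6 by randomisation stratified by district and/or constrained on one or two annex I variables, such as health-worker-covered population. Add UC-level baseline stunting if baseline data are available before allocation, and state the order of survey, recruitment and allocation. Define the acceptable allocations in advance, draw one of them at random, and carry every stratification and constraint variable into the analysis.

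The cost is wording, brief programming, and one to three of the 12 − 2 = 10 between-cluster degrees of freedom. If three are spent, the two-sided 5% t value rises from 2.23 (10 df) to 2.36 (7 df), about 6%, so only variables expected to predict stunting are worth using. No extra participants or measurements are needed. If baseline stunting is used, allocation must wait for those data, which affects the timing of training, registration and first distribution. If that delay is unacceptable, district and annex I variables alone can be used, with a smaller gain.

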## Study Site and eligibility criteria

According to the implementation plan of WFP, the project will be operating in 29 Union Councils (UCs) in Thatta and Sajawal districts. The UCs were selected on the basis of LHW´s presence, since they are the main implementing partners. The project aims to reach children 6-23 months, children 24-59 months and PLW.

Inclusion criteria for children and mothers are defined as follows:

**Children 6-23 months:** All eligible children between 6-23 months in the catchment area will be enrolled for food supplements, independent of nutritional status and age. This group will receive Wawamum during the programme period.

**Children 24-59 months:** All eligible children between 24-59 months in the catchment area will be enrolled for food supplements, independent of nutritional status and age. This group will receive MNPs during the programme period.

**Pregnant and lactating women:** All pregnant women will be enrolled in the project, regardless of the month of pregnancy and nutrition status. The programme will try as much as possible to engage women at earliest stage of the pregnancy. Similarly all lactating women in the first six months after giving birth will be engaged, covering the exclusive breastfeeding period. It is also being discussed whether it will be important a screening to identify overweight or obese women and what would be the approach in such cases.

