**Methodology and Study Design:**

The effectiveness of the project will be measured in terms of the impact of the proposed interventions on the stunting and micronutrient deficiency prevalences in the target group (children and mothers). Given the conditions of project implementation, a quasi-experimental “double difference” design would be appropriate to assess the impact of the intervention. We propose to compare the intervention and non-intervention (control) groups before (first difference) and after the intervention (second difference).

Then, the operational implementation of the research comprises a baseline and end line surveys. In addition, a nested cluster randomized controlled trial will be implemented to track the evolution of key variables related to the quality of intervention delivery and intermediate nutrition outcomes. The control clusters will receive routine public and private health services available in the area. The overall research design is shown in Figure 1.

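### The cluster trial confines its intervention sample to 6 union councils although the programme runs in many more; spreading the same sample over about 12 would gain about 5 to 8 points of power but would not reach the stated 80%

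*Protocol*

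**What the plan says.** Under Study Site and eligibility criteria, the protocol states that "the project will be operating in 29 Union Councils (UCs) in Thatta and Sajawal districts". The Study site section of the evaluation adds: "The LHW catchment area of 29 targeted union councils of these districts will be in the intervention group". It places the uncovered remainder of those same UCs in the control group.

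For the nested trial, Sample Size Estimation states that "A union council has been taken as the cluster for the estimation of sample size for RCT". The sample comes from "12 union councils which will be randomly selected from the list of 29 union councils", divided as "6 union councils for intervention group and 6 union councils for control group". Of the cohort aged 6-23 months it says: "A sample size of 70-75 children per cluster was estimated with a statistical significance of 0.05, power of 0.80, and an intra-cluster correlation of 0.02". The totals are 900 children aged 6-23 months, 1,100 aged 24-59 months and 2,000 pregnant and lactating women. That is 450, 550 and 1,000 per arm, or about 75, 92 and 167 per UC.

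Methodology and Study Design says of the comparator: "The control clusters will receive routine public and private health services available in the area". Trial participants "will be identified through the baseline survey being done in the targeted union councils". The protocol gives no reason for stopping at 6 intervention UCs.

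**The concern.** In a trial with few clusters, the number of clusters limits precision. If 6 whole UCs are drawn at random from 29 as controls, the other 23 are a random complement. Any random selection of them is then a valid randomised intervention arm, and the programme reaches them whether or not the trial measures them. Concentrating 450, 550 or 1,000 participants in 6 UCs leaves the between-UC variance of the intervention arm higher than it needs to be. The variance could be reduced without more participants, without another UC kept off the programme, and without touching the control arm. Stunting is the primary outcome, so a loss of power here bears on the trial's main result.

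**Working it through.** **Inputs.** Stated in Sample Size Estimation: 6 UCs per arm, 450 / 550 / 1,000 participants per arm, ICC 0.02 (for the two child cohorts only), alpha 0.05, power 0.80, a 10% difference in stunting and a 25% difference in low birth weight. Assumed because the trial section does not give them: control stunting 49% (borrowed from the survey sample size), 10% read as absolute, a two-sided test, low birth weight 25% v 18.75% with ICC 0.02, the same ICC in both arms, and no losses.

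**The plan's own figure.** For 49% v 39%, two-sided, 80% power, the unclustered size is 386 per arm. With 75 per UC the design effect is DE = 1 + 74 × 0.02 = 2.48, so 386 × 2.48 = 957 per arm, or 957/75 = 12.8 UCs per arm. The plan has 450 and 6. Solving n[1 + (m − 1)ICC] = km gives m(k − n × ICC) = n(1 − ICC). Since 386 × 0.02 = 7.7 exceeds 6, no cluster size reaches 80% with 6 UCs per arm. The stated figure is not reproduced under these inputs.

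**Spreading the intervention arm.** N per arm is fixed, with 6 control UCs and k1 intervention UCs:

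Var = p1(1 − p1)[1 + (N/k1 − 1)ICC]/N + p0(1 − p0)[1 + (N/6 − 1)ICC]/N

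Power is two-sided from the non-central t. Welch df = (v1 + v0)²/[v1²/(k1 − 1) + v0²/5], where v1 and v0 are the two terms of Var.

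For 6-23 months, v0 = 0.2499 × 2.48/450 = 0.001377. The intervention term is:
- k1 = 6: 0.2379 × 2.48/450 = 0.001311
- k1 = 12 (37.5 per UC, DE 1.73): 0.000915
- k1 = 23 (19.6 per UC, DE 1.37): 0.000725

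| Cohort | k1 | SE | Welch df | Power |
|---|---|---|---|---|
| 6-23 months | 6 | 0.0518 | 10.0 | 41.4% |
| | 12 | 0.0479 | 11.5 | 48.2% |
| | 23 | 0.0458 | 11.0 | 51.2% |
| 24-59 months | 6 | 0.0500 | 10.0 | 44.0% |
| | 12 | 0.0458 | 11.4 | 51.5% |
| | 23 | 0.0437 | 10.6 | 54.7% |
| Low birth weight | 6 | 0.0383 | 9.9 | 31.4% |
| | 12 | 0.0348 | 10.1 | 36.9% |
| | 23 | 0.0330 | 8.9 | 39.3% |

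**Range.** For 6 / 12 / 23 intervention UCs with Welch df, 6-23 months unless noted:
- ICC 0.01: 55 / 61 / 64%
- ICC 0.05: 25 / 30 / 32%
- 30% v 20%, ICC 0.02: 51 / 58 / 60%
- 10% read as relative (49% v 44.1%), ICC 0.02: about 13.6 / 15.5 / 16.4%
- Low birth weight with ICC 0.01: 47 / 53 / 56%

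**More participants in the same 6 UCs.** Matching the 12-UC standard error of 0.0479 within 6 intervention UCs takes about 2,000 intervention children instead of 450. With unlimited children in 6 UCs, v1 tends to 0.2379 × 0.02/6 = 0.000793 and SE = √(0.001377 + 0.000793) = 0.0466. That is still above the 0.0458 from 450 children in 23 UCs.

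**Ceiling.** Even with one intervention child per UC, v1 = 0.2379/450 = 0.000529 and SE = √0.001906 = 0.0437. The normal approximation, which is generous here, then gives about 63%.

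**The case against.** **The premise is inferred.** The protocol says the 12 UCs are randomly selected but does not describe how they are split between arms. Read literally, the Study site section supplies the covered areas of all 29 UCs and takes controls from the uncovered remainder. If the trial's controls follow that rule, further UCs are not a randomised comparator. This stands as a condition: the passages must be reconciled before the change is made.

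**The size is modest.** With pooled degrees of freedom (k1 + 4), a reader would get 50% and 56% at 6-23 months for 12 and 23 UCs. Those figures are too favourable. The 6 control UCs dominate the variance, so degrees of freedom stay near 9 to 11.5 however many intervention UCs are added. If 10% is relative, almost nothing is gained.

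**The cost is more than travel.** Transportation of Commodities has the third party monitor delivery in the UCs selected for the trial, and monthly compliance visits and quarterly rounds follow every participant. The protocol also presents the trial as in-depth work on a subset. This is fair and belongs in the trade-off.

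**Two stronger readings are not supported.** A reader might infer that spreading the sample would restore the stated 80%; the ceiling above shows that it cannot. A reader might also divide the survey's 4,200 households by 29 to count potential recruits per intervention UC. The documents do not support that, because the 4,200 span both survey groups, their split is not stated, and sampling is in two stages.

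Equal allocation of 6 and 6 is not an error or a contradiction in itself. None of this removes the direction of the effect, which holds for any ICC above 0.

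**Conclusion.** The point holds as a partial efficiency gain, not as a repair of the trial's power. With the same participants and 6 control UCs, moving from 6 to 12 intervention UCs adds about 7 points at 6-23 months, 7 to 8 at 24-59 months and 5 to 6 for low birth weight. It adds about 2 points if the 10% is relative. Going on to 23 UCs adds only about 2 to 3 points more in each cohort under the main assumptions. These levels rest on a borrowed 49% control rate, a two-sided test, an absolute 10 points for the child cohorts, and an assumed rate and ICC for low birth weight. The gain also requires that the 6 control UCs be a random draw of whole UCs. Separately, 6 UCs per arm does not give the stated 80% under these inputs, so the power statement needs correction whether or not the sample is spread.

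**What to change.** 1. In Sample Size Estimation, restate the power. Give the control rate, whether 10% is absolute or relative, the sidedness, and the rate and ICC for low birth weight. Say plainly what 6 control UCs can deliver.

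2. State that the 6 control UCs are a random draw from the 29, and reconcile this with the Study site section, which places the covered areas of all 29 in the intervention group.

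3. Recruit the same intervention totals from about 12 randomly chosen intervention UCs: roughly 37-38, 46 and 83 per UC in the three cohorts, instead of 75, 92 and 167. Leave the control arm as planned.

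4. Specify an analysis that respects the UC as cluster, allows unequal cluster numbers and uses small-sample (Welch-type) degrees of freedom.

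The cost is protocol wording, plus monthly and quarterly rounds and third-party delivery monitoring in 6 more UCs. No extra participants are needed, and no further UC goes without the programme. If the field cost is judged too high for 5 to 8 points, item 3 can be declined with a stated reason; items 1 and 2 are still needed.
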